## 5. BACKGROUND AND RATIONALE

Chronic kidney disease (CKD) is increasingly common, affecting around 10% of the entire population, associated with an age-related decline in renal function that is accelerated in hypertension, diabetes mellitus, obesity and primary renal disorders. While this high (and rising) prevalence is in part due to the ageing population, it is also a result of increases in hypertension and diabetes mellitus as well as a variety of primary renal disorders. CKD is defined and categorised in to 5 stages using glomerular filtration rate (GFR) as well as evidence of renal damage (imaging or proteinuria) in the early stages. The largest group, with over 50% of cases, is CKD stage 3, defined as a GFR of 30 to 59 ml/min/1.73m^2. Population studies have used the four variable Modification of Diet in Renal Disease (MDRD) formula to determine estimated GFR (eGFR) [1]. In patients aged 65 or over, up to 35% have an eGFR of less than 60 mls/min/1.73m^2 [2]. CKD prevalence appears to be increasing, rising from 10% to 13% over the last decade in one large cohort in the United States [3].

### *CKD and risk of cardiovascular disease*

CKD is a major cause of increased mortality and morbidity through increased vascular events and progression to end stage renal failure (ESRF) [4]. These increased events result in CKD having high cost to healthcare systems, with the dialysis required in ESRF benchmarked as at the maximum acceptable cost effectiveness threshold for an intervention by most healthcare systems. However, the most important component of CKD in terms of mortality and morbidity is cardiovascular disease (CVD) [5]. There is a graded inverse relationship between cardiovascular risk and eGFR, independent of age, sex and other riskfactors [6-9] or for creatinine [10]. While the cardiovascular risk of end-stage CKD is extreme, in public health terms the burden resides in early stage (CKD stages 1-3) disease, which is more prevalent, affecting around 40% of those over 70 years. When added to conventional risk factors, renal markers substantially improve risk stratification and CKD is therefore an important and under-recognised risk factor for CVD in the general population [11].

Although the risks of myocardial infarction and other manifestations of coronary artery disease are increased in CKD, the pattern of CVD is atypical, with a much greater incidence of heart failure and sudden cardiac death than in the general CVD population [12-14]. The main pathological features in CKD that appear to determine this particular cardiovascular risk phenotype are:

- a. Left ventricular hypertrophy and fibrosis accompanied by both systolic and diastolic dysfunction: there is a very high prevalence of left ventricular hypertrophy (LVH) in CKD, often accompanied by magnetic resonance imaging evidence of fibrosis, with LVH in over 30% of patients in stage 2 CKD (eGFR 20-29) and Stage 3 CKD (eGFR 30-59) and in 80% of patients at the start of renal replacement therapy [15-17]. Importantly, the increase in LV mass is a strong independent predictor of mortality in CKD (as in non-CKD states) and regression of LVH is associated with improved cardiac outcome.
- b. Arterial wall thickening, stiffening and calcification (atherosclerosis). Large conduit arteries buffer the changes in pressure resulting from intermittent ventricular ejection. Stiffening of the arteries (loss of arterial compliance) leads to increased systolic and pulse pressure, and the resultant increase in afterload is a major cause of LVH and its progression over time [18-20]. Prospective studies have demonstrated that measures of aortic stiffness, such as aortic pulse wave velocity (PWV), and augmentation of central aortic pressure by early wave reflections (Aix), are strong independent predictors of all-cause and cardiovascular mortality in patients on dialysis [21, 22] and lowering aortic PWV, mainly by use of an ACE-inhibitor, is associated with an improved survival in

dialysis patients [23]. In the latter study, the reduction in aortic PWV was associated with a parallel reduction in mean arterial and pulse pressure in survivors. In contrast, in those dying from cardiovascular events neither pulse pressure nor aortic PWV were significantly modified by ACE inhibition, although mean arterial pressure (the usual measure in clinical practice) was lowered to the same extent as in survivors. All these data suggest that arterial stiffness is not merely a marker of arterial damage but a potentially reversible factor contributing to mortality.

Therefore, although patients with CKD also suffer typical patterns of cardiovascular disease (coronary and peripheral artery atherosclerosis), the excess rates of cardiovascular events in CKD appear to relate more to vascular wall and ventricular changes than to atherosclerosis. The causes of atherosclerosis and LVH in CKD are complex but it is likely that as renal function declines, the onset of sodium overload combined with hypertension, chronic anaemia, oxidative stress and activation of the renin-angiotensin-aldosterone system (RAAS) and sympathetic nervous system all contribute to this development of atherosclerosis, myocardial hypertrophy and fibrosis. Furthermore, many of these factors cause vascular endothelial dysfunction which as well as leading to atherosclerotic disease is a major functional component of arterial stiffening [16]. It is the early development of arterial stiffening, causing loss of arterial compliance, increased afterload and exposure of end organs to high phasic pressures, which is thought to be a key factor in the causation of left ventricular hypertrophy and small vessel damage in the brain and kidney [15].

Given this particular vascular pathophysiology, it is unsurprising that conventional cardiovascular risk factors are less predictive of outcomes in CKD than in the general population, [24] and much less predictive than eGFR and protein excretion [6, 9, 25], even after controlling for variables such as blood pressure [17]. Furthermore, interventions to reduce the increased cardiovascular risk in CKD have proved disappointing, with only limited evidence for traditional therapies in terms of cardiovascular outcomes. For example, the SHARP (Study of Heart and Renal Protection) trial [26] aimed to assess the safety and efficacy of reducing LDL cholesterol in more than 9000 patients with chronic kidney disease with a low dose of a statin (simvastatin 20 mg daily). The trial showed that lowering of LDL cholesterol safely reduced the risk of major atherosclerotic events in patients with CKD. However, the reduction in non-fatal myocardial infarction or coronary death was not significant. There are also limited therapeutic options for the prevention of further renal functional decline. Presently, the only interventions shown to reduce or prevent renal function decline for most patients with CKD is avoidance of renal damage (e.g. treating infections and avoiding NSAIDs in at-risk people), and effective treatment of risk factors, namely hypertension and diabetes mellitus (DM). In addition, drugs acting on the RAAS system offer modest additional benefits to blood pressure (BP) lowering alone in patients with diabetic nephropathy with proteinuria [27].

Better treatment options to provide protection from vascular events or delay progression of CKD are therefore urgently needed, especially given the increasing burden of the disease. Desirable clinical outcomes for any new therapies would be effective and safe reduction of cardiovascular events and premature death and/or delay in progression of renal decline. The most important target CKD population for such preventive interventions are those with CKD stage 3b (eGFR 30-44 ml/min/1.73m^2), since this has high prevalence at 3%, represents progressive renal disease, and is associated with a 12-fold increase in cardiovascular disease (CVD), compared to those with eGFR above 60. In contrast, relative cardiovascular risk is 2 fold in CKD 3a (eGFR 45-59), though the prevalence is nearer 15% [6]. Important new candidates for potential cardio-protection in CKD are drugs that act on the aldosterone pathway of the RAA system.

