## 12.3. Sample Size Determination

A UK representative spread of practices will be achieved by stratifying practice postcode location into quartiles of Townsend Deprivation Score and selecting practices that agree to take part sequentially until each deprivation quartile practice target is reached. This strategy will most probably ensure that populations selected will also be representative for ethnicity but the sequential practice selection strategy will be examined after ten practices have been selected for each deprivation quartile to ensure practices serving high proportions of ethnic minorities are included in the final five places, if this has not already occurred in the earlier selections.

The estimate for the cardiovascular (CV) event rate (defined by hospitalisation for coronary heart disease, heart failure, ischemic stroke and peripheral arterial disease) and total mortality rate in patients with CKD 3b (eGFR 30-44 ml/min/1.73m^2) being 11.29 and 4.76 per 100 person years respectively gives a combined

event rate of 16.05 per 100 person years [5]. In those with eGFR in the range 45-50 ml/min/1.73m^2, the event rate is conservatively estimated to be 0.667 times as high (10.7 events per 100 person years[76] and we assume half the participants will fall in this range giving an overall event rate of 13.4 events per 100 person years. To detect a 20% relative risk reduction in death or cardiovascular events within 3 years in the intervention group as compared with the control group (i.e. hazard ratio=0.8) with an anticipated treatment withdrawal rate of 13% (which gives a diluted estimated treatment effect = 0.84) and a two sided significance of 0.05, 1511 participants per group (3022 total) are required at 80% power and assuming 10% attrition rate.

We have decided to power the trial conservatively on a 20% risk reduction since this proposed treatment effect is around half the risk reduction observed in the ARA mild heart failure trial (EMPHASIS). The estimated hazard ratio in the EMPHASIS eplerenone versus placebo mild heart failure trial (only mildly symptomatic patients were included) were 0.63 (CI 0.54-0.74, p<0.001) for the composite endpoint of death from CV causes or hospitalisation for heart failure at the median follow up of 21 months. The conservative upper CI for the treatment effect was 26% reduction. The placebo CV event rate in EMPHASIS trial was similar to observational data on CV events in CKD 3b patients [5].

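### The 0.667 event-rate factor for eGFR 45-50 is called conservative, yet it conflicts with the protocol's own 12-fold and 2-fold risk figures; if those figures are right, the stated 80% power is about 65-76%

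*Combined protocol and SAP*

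**What the plan says.** Protocol section 5, under the heading on CKD and cardiovascular risk, names stage 3b (eGFR 30-44) as the population to treat. One reason is "since this has high prevalence at 3%, represents progressive renal disease"; another is a "12-fold increase in cardiovascular disease (CVD), compared to those with eGFR above 60. In contrast, relative cardiovascular risk is 2 fold in CKD 3a". The 2-fold figure is for eGFR 45-59 and is cited to reference 6.

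Protocol 12.3 starts from stage 3b rates for cardiovascular hospitalisation and for death, "being 11.29 and 4.76 per 100 person years respectively gives a combined" "event rate of 16.05 per 100 person years [5"]. For the added band of eGFR 45-50, "the event rate is conservatively estimated to be 0.667 times as high (10.7 events per 100 person years[76"]. It continues: "we assume half the participants will fall in this range giving an overall event rate of 13.4 events per 100 person years". The target is a "20% relative risk reduction in death or cardiovascular events within 3 years in the intervention group", diluted for 13% treatment withdrawal. This gives 1511 per group at 80% power with 10% attrition.

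SAP 2.4 repeats the rates, the 0.667 and the word conservatively, without the citations.

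**The concern.** An event-rate assumption is conservative when it errs low. Section 5 implies that cardiovascular risk in stage 3a is one sixth of that in stage 3b; the sample size puts the lower part of stage 3a at two thirds. Set against the protocol's own rationale, 0.667 errs high.

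The sourcing adds to the doubt. By its title in the reference list, reference 5, behind the stage 3b rate, concerns death, cardiovascular events and hospitalisation. Reference 76, behind the factor, concerns mortality and end-stage renal disease. Yet the factor multiplies a composite that is 11.29/16.05 = 70% cardiovascular hospitalisation, and neither document says which outcome 0.667 describes.

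Half the sample carries this factor, so it feeds directly into the expected events and the stated power. A null result will be read against that power.

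**Working it through.** **Inputs.** Protocol 12.3: 11.29 (cardiovascular) + 4.76 (death) = 16.05 per 100 person-years at eGFR 30-44; factor 0.667; half the participants at 45-50; HR 0.80; 13% withdrawal; 3 years; two-sided 0.05; 10% attrition; 1511 per group. Section 5: 12-fold and 2-fold.

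**Reproducing the plan.**
- Rate: 16.05 x 0.667 = 10.7; (16.05 + 10.7)/2 = 13.4.
- Dilution on the log scale: 0.80^0.87 = 0.8235.
- Events (Schoenfeld): 4(1.96 + 0.842)^2/(ln 0.8235)^2, about 834.
- Three-year event probabilities, 1 - exp(-3 x rate): 0.331 for control and 0.282 for treated, mean 0.306.
- Per group: 834/(2 x 0.306)/0.9, about 1513. This matches 1511.

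The printed diluted HR of 0.84 does not reproduce 1511 by this method: it gives 1859 per group, or 71% power at 1511. That is a separate issue, so 0.8235 is used below.

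**What section 5 implies.** For stage 3a as a whole, 2/12 = 0.167. Section 5 gives no value for 45-50. Log-linear interpolation at eGFR 47.5, between 12-fold at 37 and 2-fold at 52, gives 0.285. This is an assumption, not a document figure.

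**Effect on rate and power.** Expected events D = 2 x 1511 x 0.9 x mean 3-year probability; power = Φ(|ln 0.8235| x √D/2 - 1.96). The two power columns treat the sample as having one averaged rate, or as a 50:50 mixture of the two bands.

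| Cardiovascular factor; treatment of deaths | Rate at 45-50 | Overall rate | Power, averaged rate | Power, mixture |
|---|---|---|---|---|
| Plan: 0.667 on everything | 10.7 | 13.4 | 80% | 80% |
| 0.167; deaths x 0.167 | 2.7 | 9.4 | 67% | 65% |
| 0.285; deaths x 0.285 | 4.6 | 10.3 | 71% | 69% |
| 0.167; deaths x 0.667 | 5.1 | 10.6 | 72% | 70% |
| 0.285; deaths x 0.667 | 6.4 | 11.2 | 74% | 73% |
| 0.167; deaths unscaled | 6.6 | 11.3 | 74% | 73% |
| 0.285; deaths unscaled | 8.0 | 12.0 | 76% | 76% |
| 0.50; deaths unscaled | 10.4 | 13.2 | 80% | 79% |

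Example, second row, mixture: the 3-year probabilities are 0.382 and 0.077 (control) and 0.327 and 0.064 (treated), mean 0.2126. Then D = 2719.8 x 0.2126 = 578, and power = Φ(0.1941 x 24.04/2 - 1.96) = 65%.

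**When could 0.667 and section 5 both hold?** Let w be the share of stage 3a lying at 45-50, and assume no excess risk at 51-59. The largest relative risk at 45-50 is then (2 - (1 - w))/w.
- If 0.667 applies to cardiovascular events, the risk at 45-50 is 12 x 0.667 = 8-fold, which needs w of at most 1/7 (14%).
- If deaths are unscaled, the planned 10.7 needs a cardiovascular factor of (10.7 - 4.76)/11.29 = 0.53, or 6.3-fold risk, so w is at most 1/5.3 (19%).
- At w = 20% the ceiling is 6-fold, a factor of 0.50. That is the last row of the table.

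**The case against.** The strongest reply is that unlike quantities are being compared. Section 5 speaks of cardiovascular risk over 45-59; the factor applies to a composite, 30% of it all-cause death, at the worse end of that range. The protocol also says that entry was widened to cover measurement error and fluctuation around stage 3b, so the added participants may resemble stage 3b more than average stage 3a. Both points stand. They are why a range is shown and why 0.29 is not an upper bound. They do not support the word conservative, because the two statements fit together only if 45-50 is a small minority of stage 3a, which the documents do not say.

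A second reply is that the 11.29 rate counts hospitalisation for coronary disease, heart failure, ischaemic stroke and peripheral arterial disease, while the endpoint adds arrhythmia, atrial fibrillation, TIA and first onset without admission. This pushes the true rate upwards. It stands, but the documents give no figure for it.

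A reader might infer that 13.4 is simply wrong. The documents do not support that: 0.667 has its own citation, and the 12-fold and 2-fold figures may be the ones in error. Supplementary Table 2 shows 5.37 per 100 years in standard care, which might look like proof. But that is a post hoc figure without peripheral arterial disease, covers all eGFR levels, and cannot isolate this factor. A reader might also start from the printed HR of 0.84 and quote 56-67% power. About nine points of that fall come from the dilution figure (80% to 71% at the plan's own rate), not from the event rate.

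**Conclusion.** The conflict is real and unreconciled, and conservatively is unsupported by the protocol's own rationale. The arithmetic from 0.667 to 13.4 is correct; the assumption is in question.

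The size is conditional on section 5. With cardiovascular factors of 0.17-0.29, the overall rate is about 9.4-12.0 rather than 13.4 per 100 person-years, and power is about 65-76% rather than 80%. This assumes a 50:50 split, constant hazards, 10% attrition and HR 0.8235. If 45-50 is only a fifth of stage 3a, the factor takes its ceiling of 0.50 and deaths are unscaled, power is about 79% and the gap nearly closes. The extra endpoint components could offset some of the loss.

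**What to change.** In protocol 12.3 and SAP 2.4:

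- Give the source value behind 0.667 and say whether it describes cardiovascular events, death or the composite.
- Reconcile it with the 12-fold and 2-fold statement in section 5, and correct whichever figure is wrong.
- Delete conservatively unless the source supports it.
- If reference 5, which supplied the 30-44 rate, reports a suitable band, take the 45-50 rate from it.
- Restate the overall event rate and the resulting power over the plausible range of factors.

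The cost is about one paragraph in each document, with no change to enrolment; the stated power may become less favourable. The printed diluted HR of 0.84 and the SAP's 1455 per arm at 90% power should be handled as separate issues.

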***Role of aldosterone in cardiovascular disease***

Blockade of RAAS with Angiotensin Converting Enzyme (ACE) inhibitors and Angiotensin II Receptor Blockers (ARBs) has shown mortality benefit in patients with chronic heart failure and in those with, or at high risk of, coronary artery disease [27-29]. The benefits are attributed to prevention of the multiple adverse effects of angiotensin II.

Aldosterone may also be an important mediator of cardiac and vascular damage in many disease states. Mineralocorticoid receptors are present in many tissues, including the brain, heart and blood vessels as well as the kidney and there is aldosterone production within these tissues [30]. These receptors may also be activated by circulating glucocorticoids in the presence of oxidative stress [31]. Local mineralocorticoid receptor activation by aldosterone leads to numerous pathological effects on the cardiovascular system including endothelial injury, inflammation, oxidative stress and fibrosis in the heart and vasculature, as well as the development of hypertension and autonomic dysfunction [30, 32, 33].

*Rationale for ARA intervention to reduce cardiovascular events:* In animal models, chronic aldosterone infusion and sodium loading results in myocardial fibrosis and ventricular hypertrophy in rats, while treatment with ARAs prevents aortic and myocardial fibrosis even in the absence of blood pressure lowering [33, 34]. In aldosterone treated stroke-prone hypertensive rats, spironolactone exerts a strong protective effect against the development of nephrosclerotic and cerebrovascular lesions [35]. In humans, studies have shown that primary aldosteronism is associated with a greater LV mass and higher risk of adverse cardiovascular events than control hypertensive populations and in patients after myocardial infarction, plasma aldosterone concentration within the normal range predicts an adverse prognosis [36-38]. A recent study of subjects undergoing coronary angiography confirmed an independent association of plasma aldosterone levels with total and cardiovascular mortality [39].

Importantly, there are reliable and large studies that show that targeting aldosterone improves outcomes in established cardiovascular disease. In heart failure, a human disease state that like CKD is characterised by sodium overload and high levels of aldosterone production, the addition of the ARA spironolactone (RALES) in severe heart failure [40], or eplerenone (EPHESUS) [41] in post infarction heart failure and in mild to moderate chronic heart failure (EMPHASIS) [42], to standard therapy including ACE inhibition, reduced mortality by 30%, which therefore has a greater impact on mortality than both ACE inhibitors and beta-blockers. Further, treatment with ARAs in addition to ACE inhibitors prevents adverse LV remodelling after myocardial infarction and effectively reduces LVH in drug resistant hypertension [43]. The mechanisms of action of aldosterone include up-regulation of AT1 receptors and direct effects on fibroblast collagen synthesis as well as decreased matrix metallo-proteinase secretion [30]. An anti-fibrotic effect of ARA therapy may also be important. After myocardial infarction circulating markers of collagen turnover and fibrosis were reduced by ARA therapy [43] and in the RALES study myocardial collagen turnover was significantly reduced by spironolactone, and the fall in the marker of this index was related to the mortality benefit [44].

***Role of aldosterone and potential for ARA in progression of renal disease***

Angiotensin Converting Enzyme inhibitors (ACE) inhibitors and Angiotensin II Receptor Blockers (ARBs) appear superior to other blood pressure (BP) lowering drugs in slowing the progression of CKD, though the effect may be marginal [27]. These agents are therefore widely recommended in international guidelines as 'Reno-protection' for CKD patients, especially those with proteinuria or diabetes mellitus.

Renal specialists have avoided use of ARA drugs because of perceived risk of azotaemia and hyperkalaemia,

though similar restrictions were applied to ACE inhibitors until outcome data were reported. There are, however, accumulating data on combined treatment with ACE and ARAs to improve renal function in patients with CKD [45]. Animal experiments have shown that aldosterone can mediate renal injury and that ARAs, such as eplerenone, effectively reduce this [46-48]. Importantly, ARAs are similarly effective in low aldosterone models of CKD probably reflecting the importance of local (paracrine) aldosterone synthesis. [49] In humans, small studies have reported that adding ARAs to ACE inhibitors or ARBs reduces proteinuria and may slow progression of renal disease [50, 51]. From a safety perspective, even oligoanuric haemodialysis patients can tolerate spironolactone in low doses [52].

### ***Diagnosis of CKD***

The current UK standard estimating equation for GFR, Modification of Diet in Renal Disease study (MDRD) [53], results in an underestimation bias for higher levels of renal function. The more recent Chronic Kidney Disease Epidemiology Collaboration (CKD-EPI) equation [54] has been validated in general populations (excluding very elderly persons) [55, 56], as well as in different ethnic groups with appropriate equation modification (as per MDRD [57, 58]) and has shown greater accuracy. The MDRD equation has some utility in cardiac risk prediction [59, 60] but CKD-EPI based CKD staging improves risk prediction [61, 62] and this may influence policy in the United States with plans to switch to CKD-EPI for GFR reporting [63]. Evidence for the optimal GFR estimation method in primary care populations has not been systematically summarised. BARACK D will measure CKD using both criteria and will provide important new comparator data to inform this debate.

